**Study Area**

**Major Areas of Knowledge**

- Major Area 4. Health Sciences

**Main Purpose of the Study**

- Clinical

**Public Title of Research:** EVALUATION OF THE EFFECTS OF CRYOTHERAPY ON RECOVERY FROM DELAYED ONSET MUSCLE SORENES IN ATHLETES AFTER HIGH INTENSITY INTERVAL TRAINING IN THE MURPH WOD IN CROSSFIT: REHEARSAL CLINICAL, CONTROLLED AND RANDOMIZED

**Public Contact**

| CPF/Document   | Name                      | Telephone  | E-mail                            |
|----------------|---------------------------|------------|-----------------------------------|
| [name] | [name] | [name] | [contact] |

**Scientific Contact:** [name]

Study Design / Financial Support

Study Design: Intervention/Experimental

Health conditions or problems

| Health Condition or Problem   |
|-------------------------------|
| Delayed onset muscle soreness |

General Descriptors for Health Conditions

ICD1-10: International Classification of Diseases

| ICD Code | CID Description        |
|----------|------------------------|
| M62      | Other muscle disorders |

Specific Descriptors for Conditions of

ICD1-10: International Classification of Diseases

| ICD Code | CID Description        |
|----------|------------------------|
| M62      | Other muscle disorders |

Type of Intervention: Experimental

Nature of Intervention

- OtherCryotherapy

Intervention Descriptors

Intervention Descriptors

| Interventions |
|---------------|
| Cryotherapy   |

Phase

- Phase 1

**There will be use of placebo or the existence of groups that will not undergo any intervention:** The use of a placebo allows a more accurate comparison between the effects of real cryotherapy and the psychosomatic responses of the participants, ensuring that any improvements observed in the intervention group are truly attributed to cryotherapy and not to the placebo effect.

Design:

Initially, we will collect baseline data from all participating athletes so that we can create a baseline. We will then use the musculoskeletal pain assessment questionnaire (E-ADOM) to assess participants' level of muscle discomfort prior to the start of training. We will then administer the Brief Pain Inventory (BPI), a tool that allows us to measure pain intensity and its impact on individuals' daily activities. In addition, the Visual Analogue Scale (VAS) will be used so that participants can indicate pain intensity on a scale of 0 to 10, providing a subjective measure of pain.

For a more objective assessment, we will use algometry, which measures pain sensitivity by applying controlled pressure to the gastrocnemius muscle. In addition, we will use thermographic imaging to observe the temperature of the gastrocnemius muscle, which may indicate inflammation or other physiological processes. Finally, we will collect blood samples to measure levels of creatine kinase (CK), an enzyme that serves as a marker of muscle damage. Analyzing these levels will provide us with important information about the degree of muscle damage caused by training.

After collecting baseline data, athletes will perform the WOD Murph, which consists of running 1 mile, performing 100 pull-ups, 200 push-ups, 300 air squats, and running another 1 mile, an intense physical activity that generates a DOMS.

After completing the training, we will perform an intervention with immersion cryotherapy. An ice bath will be provided, in which the athlete will enter covering the entire gastrocnemius muscle. The application of ice to the participants' muscles aims to reduce inflammation and pain, promoting faster recovery.

To evaluate the effects of the cryotherapy intervention, we will repeat the collection of all data collected pre-workout at 24, 48 and 72 hours after training for possible conclusions.

Financial Support

| CNPJ | Name | E-mail | Telephone | Type             |
|------|------|--------|-----------|------------------|
|      |      |        |           | Financing
Own |

Keyword

| Keyword                          |
|----------------------------------|
| high intensity interval training |
| delayed onset muscle soreness    |
| cryotherapy                      |

Study Details

Summary:

Currently, more than 30% of the world's population is physically inactive, and one of the main reasons is time constraints. This fact has significant implications for global health, suggesting recommendations for shorter and more effective exercises, such as high-intensity interval training (HIIT). This type of training has the ability to improve aerobic fitness, body composition, and cardiometabolic health. An example of HIIT is the CrossFit® "Murph" workout, which combines aerobic and resistance modalities in intense circuits. The CrossFit "Murph" workout, one of the most challenging, often results in delayed onset muscle soreness (DOMS). Thus, ice immersion (cryotherapy) stands out as a viable therapeutic modality to study, due to its anti-inflammatory and analgesic effects promoting rapid recovery after exercise. Therefore, the present study aims to analyze the effect of cryotherapy as an intervention in the recovery of DOMS after practicing the HIIT of the CrossFit® Murph workout of the day (WOD). This study is a randomized controlled clinical trial, in which participants are divided into control (CG) and intervention (IG) groups. Assessment instruments include the visual analogue pain scale (VAS), BORG scale, brief pain inventory (BPI), questionnaire for assessing musculoskeletal pain in exercise practitioners (Q-ADOM), algometer, thermographic camera and collection of blood samples to assess creatine kinase CK. The results are expected to contribute to the development of more precise intervention protocols with cryotherapy in DOMS.

Introduction:

More than 30% of the world's population is physically inactive, which has significant implications for global health (Hallal et al., 2012). There is now growing recognition that the time constraints faced by many people when initiating exercise programs make previous recommendations unfeasible, suggesting that shorter intervals of time may be more appropriate (Molanorouzi et al., 2015). Furthermore, high-intensity exercise has been shown to provide improved outcomes in terms of strength and cardiorespiratory fitness (Garber et al., 2011). High-intensity interval training (HIIT) is generally defined as the repetition of short or long bursts of intense exercise, interspersed with periods of active or passive recovery. However, there is no consensus on the specificity, frequency, and duration of exercise required to maximize health benefits and prevent diseases associated with a sedentary lifestyle (Gillen and Gibala, 2014). This type of training can improve aerobic fitness, body composition, and cardiometabolic health in diverse populations (Babraj et al., 2009). HIIT training is generally recommended to be performed with full-body exercises and cyclic movements, such as walking, running, swimming, or cycling, which do not significantly increase muscle strength or power (Waller et al., 2011). Multimodal training combines several modalities, such as aerobic endurance, strength, and circuit training. There is some evidence that continuous circuit training can induce a cardiovascular response, but the intensity used generally varies from low to moderate (Hunter et al., 2003). According to McRae et al. (McRae et al., 2012), there is limited evidence that low-volume HIIT may be as effective as continuous aerobic training in improving aerobic capacity and superior muscular endurance gains, although this method has not yet been widely investigated. An example of HIIT is CrossFit®, which is a high-intensity, multimodal workout that incorporates functional (multi-joint) movement patterns performed in a circuit format, with short pauses or rest periods between exercises or sets of exercises (Bergeron et al., 2011). Since 2013, HIIT has been one of the three largest global fitness trends, with CrossFit® being a major contributor to this popularity, according to the ACSM's annual survey (Thompson, 2016). According to Wood (Wood et al., 2022), CrossFit® is effective in improving cardiovascular fitness and body composition in exercisers of all fitness levels. However, the CrossFit® methodology has also faced criticism for not strictly following established training principles, and there is little research on the specific responses to different types of training within this methodology. The International Association for the Study of Pain (IASP) defines pain as an unpleasant sensory and emotional experience associated with, or similar to, actual or potential tissue injury (DeSantana et al., 2020). In this context, delayed onset muscle soreness (DOMS) consists of the sensation of pain or discomfort in the muscles that typically increases in intensity in the first 24 hours and peaks between 24 and 48 hours after exercise (Cheung et al., 2003). This type of pain is a signal that the muscles are adapting in response to intense physical activities, especially those that involve eccentric contractions, such as the lowering phase of squats, weightlifting in strength training, or downhill running. During these activities, blood levels of creatine kinase (CK) increase, indicating muscle damage. A notable example of a workout that can induce DOMS is the "Murph," one of CrossFit's most iconic workouts, known for its physical and mental demands. Created in memory of Lieutenant Michael P. Murphy, a US Navy SEAL killed in action, this Workout of the Day (WOD) consists of running 1 mile (1.6 km), performing 100 pull-ups, 200 push-ups, 300 air squats, and running another 1 mile (1.6 km). The goal is to complete the workout in the shortest possible time, and it is a high-intensity aerobic exercise that is influenced by anaerobic performance and the recovery capacity of high-intensity exercise (Carreker and Grosicki, 2020). Due to its intensity and high volume of exercise, Murph can induce DOMS, often making subsequent workouts difficult due to discomfort. Analyzing the occurrence of DOMS and its effects after the Murph WOD, a high-intensity activity, is essential. Recovery (known as recovery) for DOMS, immediately after training as an intervention measure, should be considered, thus improving strategies for recovery of athletes. Our project aims to understand how ice immersion applied immediately after the practice of this intense activity can minimize DOMS. Ice immersion (cryotherapy) stands out as a viable therapeutic modality to study. Several studies indicate that cryotherapy can reduce inflammation and delayed onset muscle soreness, promoting faster recovery after HIIT. For example, a study conducted by Leeder et al. (Leeder et al., 2012) demonstrated that cold water immersion can reduce delayed onset muscle soreness and accelerate muscle recovery. Furthermore, cryotherapy is widely used and accepted in sports settings, and there is a significant body of research supporting its efficacy (Alexander et al., 2021). Therefore, investigating ice immersion may provide relevant and applicable data to improve athletes' recovery after high-intensity activities such as WOD Murph. Thus, this scientific project aims to fill gaps in knowledge about DOMS after performing HIIT in WOD Murph in CrossFit, also verifying whether pain persists with the intervention. It is expected that the results of these investigations will contribute to the development of more effective therapeutic protocols and significant improvements in the training quality of athletes affected by this painful condition.

Hypothesis:

The hypothesis of the study is that the application of immersion cryotherapy after performing the intense CrossFit® "Murph" workout will significantly reduce delayed onset muscle soreness (DOMS) and inflammation, promoting faster and more efficient recovery in

athletes, compared to those who do not receive cryotherapy intervention.

**Primary Objective:** To

investigate the effects of cryotherapy as a recovery intervention on the manifestation of DOMS in athletes after performing intense physical activities in CrossFit.

**Secondary Objective:** To

verify the intensity of pain perceived in DOMS after intense training, Murph, using the algometer as a research method. To verify if DOMS alters the analgesic perception in the VAS and BPI after Murph training. To verify if DOMS alters the perception of musculoskeletal pain with the Q-ADOM questionnaire after Murph training. To evaluate the levels of protein kinase CK as a biomarker of DOMS after Murph training. To verify through thermography if there is a change in muscle temperature before and after training.

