Assessment Questionnaire for Application of the Protocol: Collects information on supplementation, diet, training frequency, use of therapeutic modalities and sleep quality. 2. Visual Analog Scale (VAS): Assesses pain intensity, graded from 0 to 10. 3. BORG: Assesses the perception of physical effort, using a scale from 0 to 10. 4. Brief Pain Inventory Scale (BPI): Assesses pain intensity and its impact on daily activities. 5. Questionnaire for the Assessment of Musculoskeletal Pain in Exercise Practitioners (Q-ADOM): Identifies the characteristics of pain and its influence on the practice of physical exercise. 6. Algometer: Measures sensitivity to pain by applying controlled pressure. 7. Thermographic Camera: Detects infrared radiation emitted by the body, visualizing the temperature of the skin surface. 8. CK Protein Quantification: Measurement of creatine kinase (CK) levels in blood as a marker of muscle damage. Intervention: The intervention will consist of cold water immersion sessions (cryotherapy) immediately following the Murph workout. The water temperature will be kept below 15°C and the duration of the immersion will be 10 minutes. The cryotherapy session will involve immersing the athletes' legs in a suitable container, ensuring that all major muscle areas involved in the exercise are treated. Experimental Procedures: Initially, baseline data will be collected using E-ADOM, BPI, VAS, algometry, thermography and blood samples to measure CK. After baseline data collection, athletes will perform the Murph WOD. After the workout, the cryotherapy intervention will be performed. Data will be collected again 24, 48 and 72 hours post-workout to assess the effects of the intervention on DOMS.

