This research is expected to contribute to more accurate protocols and assessment methods for DOMS. It will provide coaches, physiotherapists, and athletes with concrete data on how to optimize post-exercise recovery, improving performance and adherence to training programs. It will also fill a significant gap in the literature regarding the effectiveness of post-exercise recovery strategies.

Sample Size in 30  
Date of First Recruitment: 08/11/2024

| Recruitment Countries          |         |                            |
|--------------------------------|---------|----------------------------|
| Country of Origin of the Study | Country | No. of survey participants |
| Yes                            | BRAZIL  | 30                         |

Other Information

Will there be use of secondary data sources (medical records, demographic data, etc.)?  
No

Report the number of individuals approached personally, recruited, or who will undergo some type of intervention at this center search:  
30

Groups into which research participants will be divided at this center

| Group ID    | No. of Individuals | Interventions to be carried out |
|-------------|--------------------|---------------------------------|
| Control     | 15                 | They will not do cryotherapy    |
| Cryotherapy | 15                 | Cryotherapy                     |

Is the Study Multicenter in Brazil?  
No

Do you propose waiving the TCLE?  
No

Will samples be retained for bank storage?  
Yes

Justification:  
Yes, samples will be retained for bank storage. Blood samples collected to measure creatine kinase (CK) levels will be stored in a biological sample bank. This storage will allow for future additional analyses that may arise as relevant to the study or to subsequent research related to delayed onset muscle soreness (DOMS) and muscle recovery. Samples will be collected following strict handling and conservation protocols, ensuring the integrity and viability of the samples for future analyses. All samples will be coded to ensure participant confidentiality and privacy, and stored under controlled conditions. temperature and safety at the Laboratory of Neuroscience, Neuromodulation and Pain Study (LANNED). Participants will be informed about the retention and storage of samples during the informed consent process, ensuring that they are aware of and in agreement with the use prolonged storage of your biological samples for research purposes.

Execution Schedule

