Correction of Pending Issues: 1. Clarify regarding the collection of biological material (blood) - location of collection and disposal of biological materials. A: The following text was included in item 5.8.8: The collection of biological material, specifically blood samples, will be carried out in an appropriate environment within the training center, where all biosafety standards will be strictly followed. The procedure will be carried out by a qualified and experienced nurse, ensuring that the collection is done in a safe and hygienic manner. The collected material will be used exclusively for the analysis of creatine kinase (CK) levels and other possible biomarkers related to the study. After the collection, the blood will be stored in specific tubes and kept under controlled conditions until analysis. Biological materials and all items used during collection, such as needles, syringes, and other disposable equipment, will be properly discarded in containers suitable for biological waste, in accordance with current regulations on the disposal of hospital waste. 2. Enter all researchers in all documents (TCLE and detailed project). A: The inclusions were made. 3. Clarify in the TCLE that the participant, after randomization, you may be allocated to a group that will undergo cryotherapy or a group that will not undergo this intervention. In the TCLE presented apparently all volunteers will undergo cryotherapy. A: It was included in item 1 of the TCLE and in item 5.8.9 of the project detailed. 4. Clarify the need for two TCLEs for this research, considering that they were attached to the Plataforma Brasil two versions of the TCLE (TCLE\_GELO.docx files), the first submitted on 06/28/24 and the other on 07/08/2024. A: A inclusion corrected on 07/08/2024, not excluding the version of 06/28/2024. However, in the present submission, these two

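### The protocol says a placebo rules out the placebo effect, but it describes only a no-cryotherapy control, so the attribution claim is unsupported

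*Protocol*

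**What the plan says.** The Protocol's form item on placebo or groups without intervention is answered with a justification for a placebo: "The use of a placebo allows a more accurate comparison between the effects of real cryotherapy and the psychosomatic responses of the participants". It concludes that this will ensure that "any improvements observed in the intervention group are truly attributed to cryotherapy and not to the placebo effect".

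The comparator is described in three other places:

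- **Hypothesis:** athletes given cryotherapy are "compared to those who do not receive cryotherapy intervention".
- **Table of groups, column on interventions to be carried out:** for the 15 controls, the entry is "They will not do cryotherapy".
- **Correction of Pending Issues, item 3:** the reply to the ethics committee concerns allocation to "a group that will undergo cryotherapy or a group that will not undergo this intervention".

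Proposed Methodology describes one study procedure after the workout: "The intervention will consist of cold water immersion sessions (cryotherapy) immediately following the Murph workout". The water is to be below 15°C and the immersion is to last 10 minutes. Neither that section nor the Design text mentions a sham immersion, another placebo procedure or blinding of participants.

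**The concern.** The placebo statement claims a property that the described design does not have. A placebo-controlled comparison can separate the specific effect of cold from the athlete's expectation of benefit, because both arms believe they may be treated. A comparison with a group that simply goes without the ice bath cannot do this.

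This matters because the target condition is soreness, and soreness is mostly measured here through the athlete. The Design text itself describes the VAS as "providing a subjective measure of pain". A difference in expectation between arms is plausible. Recruitment includes presentations on the aims and importance of the study, the Benefits section names less soreness as a possible gain, and an athlete in an ice bath knows it. If the statement stays, a favourable soreness result could be reported as shown not to be a placebo effect when nothing in the design supports that.

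**Working it through.** The protocol gives no figure on this point to reproduce. The question is settled by setting its statements side by side, followed by a count and an illustration.

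**1. Statements compared**

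| Place in Protocol | Control condition stated or implied |
|---|---|
| Form item on placebo | A placebo |
| Hypothesis | No cryotherapy |
| Table of groups | No cryotherapy; no other procedure listed |
| Correction of Pending Issues, item 3 | No cryotherapy |
| Design; Proposed Methodology | Only the cold immersion is described; no sham, placebo or participant blinding |

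One statement invokes a placebo. All three descriptions of the comparator omit one, and the procedural text contains none.

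**2. What the comparison estimates**

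Write the mean outcome under cryotherapy as control mean + S + E. S is the specific effect of cold. E is the effect of knowing that one is treated, relative to knowing that one is not.

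- Against a credible placebo: difference = S.
- Against no cryotherapy, unblinded: difference = S + E.

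The attribution claim needs the first line. The described design gives the second, and no other arm or measurement allows E to be subtracted.

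**3. Outcomes exposed**

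Six measures are taken at baseline and repeated at 24, 48 and 72 hours: Q-ADOM (called E-ADOM in places, taken here as the same instrument), BPI, VAS, algometry, thermography and CK. The first three are self-report. Algometry applies controlled pressure but records pain sensitivity, so it also depends on the athlete's response. That makes 4 of 6. CK and the thermal image do not depend directly on report.

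**4. Illustration of scale (E is assumed)**

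Inputs: 15 per group and significance at 0.05, both from the Protocol. Assumptions: a two-sided, two-sample t-test on a score with common SD, S = 0, and E = d SD in favour of cryotherapy. The values of d are not in the document.

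Noncentrality = d × √(n/2) = d × √(15/2) = 2.739 × d, with 28 degrees of freedom.

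| Assumed d | Noncentrality | Chance of a significant result |
|---|---|---|
| 0 | 0 | 5% |
| 0.2 | 0.55 | about 8% |
| 0.3 | 0.82 | about 12% |
| 0.5 | 1.37 | about 26% |
| 0.8 | 2.19 | about 56% |

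The table shows how the risk grows with d. It does not estimate d.

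**The case against.** **The form field.** Its heading covers either a placebo or a group without intervention, so an untreated group was a permitted answer. The hypothesis already states the comparison correctly, and no sample-size input or analysis depends on the placebo sentence. All of this stands, and it means that the error lies in the description and the claim, not in the randomised comparison. But the text entered justifies a placebo and rests a causal attribution on it, and for the design described that is wrong as written.

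**How far the control descriptions go.** A reader might infer that the documents prove that controls receive nothing at all and that blinding is impossible. They do not go that far. Each description says only what the control does not get, and a control given some other procedure would fit all three. The detailed project is not shown. Even so, an untreated control is much the likelier reading: the table has a column for interventions and lists none for controls, and the ethics reply points to item 5.8.9 of the detailed project for "a group that will not undergo this intervention". An analysis plan, if one exists, could not supply a placebo arm.

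**The numbers.** The illustrated error rates rest on assumed expectation effects, so they show sensitivity and not a demonstrated bias. That stands too. The conclusion follows from comparing the statements and does not need them.

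**Conclusion.** The concern holds in this form: the protocol asserts a placebo and an attribution that its described comparator cannot deliver. As described, the trial estimates cryotherapy including expectation against no cryotherapy. The claim that benefit is not a placebo effect is unsupported, above all for VAS, BPI, Q-ADOM and algometry. The size of the expectation component cannot be derived from the document and cannot be separated from the treatment effect. The conclusion assumes that no placebo procedure is set out in material not shown.

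Two stronger readings should be resisted.

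- A reader might infer that a comparison with no cryotherapy is invalid, or that any benefit seen would be placebo. Neither follows. The comparison answers a legitimate, narrower question.
- A reader might infer that CK and thermography give an expectation-free check on the pain result. They do not. The Protocol presents CK as a marker of muscle damage and thermography as skin-surface temperature, and neither measures soreness. The Summary credits cryotherapy with both anti-inflammatory and analgesic effects, so a real analgesic effect could leave CK unchanged, and a CK difference would not show that the soreness result is free of expectation. Athletes who know their arm may also behave differently over the 72 hours.

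**What to change.** Reconcile the placebo item with the Hypothesis, the table of groups and the ethics reply.

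- If a placebo procedure exists, describe it in Proposed Methodology and in the table of groups, and say who is blinded.
- Otherwise, delete the placebo and attribution text. State that the control is no cryotherapy and that participants are not blinded. Limit the planned conclusion to cryotherapy, including expectation, versus no cryotherapy.

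As a cheap addition, state that CK assays and thermogram readings are done under codes that conceal the arm. The existing sample coding does not settle this: the Protocol gives its purpose as confidentiality and privacy and does not say that the assayist is masked. Report these two outcomes as supportive and less dependent on expectation.

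The cost is a narrower claim, some rewording, and minor work to code samples and images by concealed arm. If no placebo procedure exists, no new arm is needed.

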**Proposed Methodology:**

Proposed Methodology: Study Design: This study will be a randomized, controlled clinical trial designed to evaluate the efficacy of cryotherapy in the recovery of delayed onset muscle soreness (DOMS) in CrossFit athletes after completing the Murph workout. Study Location and Population: The study will be conducted at the Capixaba training center, with support from the Laboratory of Neuroscience, Neuromodulation and Pain Study (LANNED), located in Alfenas, Minas Gerais. The study population will consist of 30 athletes who participate in training at the Capixaba box. Sample: Thirty athletes who participated in the Murph training at the Capixaba box will be selected. Participants will be recruited through invitations made directly at the Capixaba box, where the athletes usually train regularly. Brief presentations will be given before or after the training sessions to explain the objectives and importance of the study, as well as the inclusion and exclusion criteria. In addition, informational pamphlets will be distributed and posters will be posted around the box, containing details about the study and contact information for the researchers. Individuals will be divided into 2 groups: the control group and the intervention group, allocated through a randomization process performed using the Research Randomizer website. Sample Randomization: Volunteers will be divided into CG and IG through randomization, using the Research Randomizer website to ensure random allocation of participants. Sample Calculation: The sample calculation will be performed according to Cariappa (2006), estimating 15 volunteers per group to ensure a statistical power of 85% (ß=0.20) and a significance level of p<0.05. Assessment Instruments: Several instruments will be used to assess the pain and recovery of participants: 1.

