Participants will receive detailed instructions on study procedures and safety measures before the intervention begins. These instructions include guidance on the importance of proper hydration, warming up and cooling down before and after workouts and the cryotherapy session. Information will also be provided on how to monitor and report any adverse effects following the sessions. In addition to immediate safety measures, a continuous monitoring system will be established to monitor participants throughout the study. This will include regular assessments of muscle pain and other symptoms using standardized methods such as the Visual Analogue Scale (VAS), the Brief Pain Inventory (BPI) and the Questionnaire for Assessment of Musculoskeletal Pain in Exercisers (Q-ADOM). The use of algometers and thermal imaging cameras will provide objective assessments of pain and inflammation, ensuring that any significant changes in participants' condition are detected early.

In the event of any adverse event or complication, participants will have immediate access to appropriate medical care. Emergency protocols will be established and professionals involved in the study will be prepared to deal with any unexpected situation.

**Data Analysis Methodology:** Initially, descriptive analyses will be performed to summarize the demographic and clinical characteristics of the participants, as well as the results of the pain measurements. To compare pain levels before and after the cryotherapy intervention, paired t-tests or repeated measures analysis of variance (ANOVA) will be used, depending on the normality of the data. If the data do not follow a normal distribution, nonparametric tests such as the Wilcoxon test will be applied.

Additionally, multiple regression analyses may be performed to identify potential factors that influence the efficacy of cryotherapy, such as age, gender, CrossFit experience, and training intensity level. Correlation analyses will be conducted to investigate the relationships between different pain assessment methods and CK levels. Statistical significance will be set at a level of  $p < 0.05$ . All data will be analyzed using SPSS 20 statistical software.

Primary Outcome:

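### The secondary objectives ask what follows the Murph, but the only stated pain comparison is before and after cryotherapy, with no analysis by arm

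*Protocol*

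**What the plan says.** The primary objective names cryotherapy. The five items under Secondary Objective do not, and none names a group:

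- Algometry: "verify the intensity of pain perceived in DOMS after intense training, Murph, using the algometer as a research method".
- VAS and BPI: "To verify if DOMS alters the analgesic perception in the VAS and BPI after Murph training".
- Q-ADOM: "To verify if DOMS alters the perception of musculoskeletal pain with the Q-ADOM questionnaire after Murph training".
- CK: "To evaluate the levels of protein kinase CK as a biomarker of DOMS after Murph training".
- Thermography: "To verify through thermography if there is a change in muscle temperature before and after training".

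Under Proposed Methodology, the athletes are randomised to two groups of 15. The intervention group is immersed immediately after the workout, and measurements are repeated at 24, 48 and 72 hours. The table of groups says of the 15 controls: "They will not do cryotherapy". The Hypothesis expects cryotherapy to reduce soreness and inflammation compared with athletes who do not receive it.

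Data Analysis Methodology gives one comparison for pain: "To compare pain levels before and after the cryotherapy intervention", by paired t-test or repeated measures ANOVA, or a nonparametric test such as the Wilcoxon if the data are not normal. It adds correlations between the pain measures and CK. No arm is named for either.

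**The concern.** As worded, the secondary objectives concern what the Murph and the resulting soreness do to each measure. The Introduction supports this reading: it calls for study of soreness after the Murph, and separately asks whether pain persists with the intervention. Those are two questions.

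No measurement is planned between the workout and the immersion, so every follow-up value in the cryotherapy arm is taken after treatment. Only the control arm shows the course after the Murph alone. The analysis text does not lead there: its before/after contrast is built around an intervention that controls never receive. An analyst following it would estimate the change in treated athletes or, reading it loosely, in all 30. If the treatment works, either would understate how far the Murph moves the measures, and the understatement would grow with the benefit of cryotherapy.

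**Working it through.** **The plan's own figure.** The sample size statement is "estimating 15 volunteers per group to ensure a statistical power of 85% (ß=0.20) and a significance level of p<0.05". It cannot be reproduced, because no effect size or SD is given. (A beta of 0.20 means 80% power, not 85%; that is a separate matter.) Only the allocation is used here: treated share w = 15/30 = 0.5.

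**Assumption.** Let D be the mean change from baseline after the Murph without treatment, and r the share of it that cryotherapy removes. The protocol gives no value for r, so a range of 0 to 50% is assumed.

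**Formulas.**

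- Control arm: D, that is 100% of the untreated change at any r.
- Cryotherapy arm only: (1 - r) × D.
- All 30 pooled: 0.5 × D + 0.5 × (1 - r) × D = (1 - r/2) × D.

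**Share of the untreated change that is reported.**

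| Assumed r | Cryotherapy arm only | Pooled | Control arm |
|---|---|---|---|
| 0 | 100% | 100% | 100% |
| 10% | 90% | 95% | 100% |
| 20% | 80% | 90% | 100% |
| 30% | 70% | 85% | 100% |
| 50% | 50% | 75% | 100% |

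**Precision.** The 95% confidence interval half-width for a mean change, in units of the SD of change with complete data, is t(0.975, n - 1)/√n:

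- n = 30: 2.045/√30 = 0.373.
- n = 15: 2.145/√15 = 0.554.

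**Does pooling hide a change?** With equal SDs, and ignoring extra spread between arms, the ratio of the pooled to the control-only test statistic is (1 - r/2) × √(30/15):

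- r = 20%: 0.90 × 1.414 = 1.27.
- r = 30%: 0.85 × 1.414 = 1.20.
- r = 50%: 0.75 × 1.414 = 1.06.

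The ratio reaches 1 at r = 2 × (1 - 1/√2), about 0.59. Over the assumed range, pooling shrinks the estimate but does not make a change harder to detect.

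**The case against.** A reader might infer that the answers to these objectives are biased downward. The documents do not support that, for four reasons.

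- Pooling is never stated. The hypothesis is comparative, an untreated arm exists, and repeated measures ANOVA could include group as a factor. The analysis set may also be fixed in a statistical analysis plan that is not shown.
- The bias needs cryotherapy to work, which is the hypothesis under test.
- Downward may be the wrong direction for algometry. If the reading is a pressure pain threshold (the protocol says only that sensitivity to pain is measured), soreness lowers it and an effective treatment raises it. Attenuated toward no change is the safer description.
- The before/after sentence covers pain levels only. For CK the protocol states correlations, so there the point rests on an objective and correlations assigned to no arm. That treatment would break the link between CK and soreness is conjecture.

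A reader might also infer that a negative answer could be an artefact of treatment. The test-statistic ratios show that this fails for pooling over the assumed range; it remains possible only for a treated-only analysis.

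Finally, the secondary objectives can be read as a loosely worded list of outcomes within the cryotherapy trial, since Proposed Methodology says the follow-up data serve to assess the intervention. That reading is possible, but it does not rescue the analysis text: the effect of cryotherapy also needs a comparison between arms, and none is stated.

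What remains is more than a missing detail. The protocol has its own analysis section, and the one pain comparison it states does not match the objectives.

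**Conclusion.** The point holds in conditional form. The secondary objectives ask about change after the Murph, while the stated pain comparison is centred on cryotherapy and nothing is analysed by arm. If cryotherapy works and the comparison is run in treated athletes, 80%, 70% or 50% of the untreated change would be reported at assumed r of 20%, 30% or 50%; if run in everyone, 90%, 85% or 75%. At r = 0 nothing is lost.

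These figures follow from 1:1 allocation and an assumed r. They are not estimates of what the trial will find, and they assume that cryotherapy acts against the change caused by the Murph. Thermography and CK share the unassigned group. The distortion of a pain-CK correlation cannot be sized from the documents. The design itself is sound on this point, because a randomised untreated arm will supply the data.

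**What to change.** In Data Analysis Methodology, state that:

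- change from baseline at 24, 48 and 72 hours is reported by randomised arm, with a group-by-time analysis;
- the control arm answers the objectives about what follows the Murph, including thermography;
- the course in the cryotherapy arm is reported separately, which answers the Introduction's question about pain persisting with the intervention;
- the effect of cryotherapy is judged between arms;
- pain-CK correlations are given by arm.

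Reporting by arm is better than restricting these measures to controls, which would discard the treated course that the Introduction also wants.

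The change takes a few sentences and needs no new data, visits or procedures. The cost is precision: the estimate of the course after the Murph alone rests on 15 athletes, so its 95% confidence interval half-width is about 0.55 rather than 0.37 SD of change. Correlations by arm likewise rest on 15 athletes each.
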